#### Secondary outcomes

*The eating disorder symptom impact scale* [48] () in its Spanish version (Carral‐Fernández et al., 2013). It is a 24-item scale that assesses eating disorder-specific caregiving experiences. Items are rated on a 5-point Likert-type scale ranging from 0 (never) to 4 (almost always). The internal consistency is good, with Cronbach’s alpha coefficients mostly superior to 0.70.

*Family assessment device—global functioning scale* [49]). It is a 60-item self-report about family functioning in terms of problem-solving, communication, roles, affective responsiveness, affective involvement, behavior control, and general functioning. Items are rated on a 4-point Likert scale ranging from 1 (completely agree) to 4 (strongly disagree). The internal consistency is good (Cronbach's alphas between 0.72 and 0.83) for the subscales, with a Cronbach's alpha of 0.92 for general functioning.

*Mastery and empowerment scale* [50]. It is a 34-item scale divided into three domains: family, service system, and involvement in the community. Items are rated on a 5-point Likert scale ranging from 1 (completely false) to 5 (completely true). Different studies have demonstrated that the psychometric properties of the FES are robust in both its original and translated versions [50–52].

*Multicultural quality of life index* [53]. The Multicultural Quality of Life Index is a culture-informed, self-rated instrument. Its 10 items cover key aspects of quality of life, from physical well-being to spiritual fulfilment. Regarding its applicability, the mean completion time was less than three minutes, and 96% of raters found it easy to use. Test–retest reliability was high (r = 0.87). A Cronbach’s alpha of 0.92 showed its internal consistency, and a factor analysis revealed a strong structure.

*The multidimensional existential meaning scale* [54] in its Spanish validation [55]. It is a 15-item scale that assesses existential meaning through three dimensions: comprehension, purpose, and mattering. Items are rated on a 7-point Likert scale ranging from 1 (very strongly disagree) to 7 (very strongly agree). The three MEMS subscales showed adequate internal consistency: Comprehension (ω¯ = 91), Purpose (ω¯ = 92), and Mattering (ω¯ = 86).

*Depression, anxiety and stress scale* [56]. It is a 21-item scale, in its short version, that measures clinical symptoms such as depression, anxiety, and stress. Items are rated on a 4-point Likert scale ranging from 0 (It did not happen to me) to 3 (It happened to me a lot, or most of the time). It shows excellent internal consistency: depression (α = 0.94), anxiety (α = 0.87), and stress (α = 0.91).

*Difficulties in emotion regulation scale* [57]. in its Spanish version [58]. In its adaptation, the authors reduced the items from 36 to 28, and they considered five scales instead six. The subscales are: lack of emotional control, vital interference, lack of emotional attention, emotional confusion, and emotional rejection. Items are rated on a Likert-type scale ranging from 1 to 5 (1 = "almost never" and 5 "almost always"). Higher scores indicate more difficulties in emotional regulation. Psychometric properties were adequate, with very good internal consistency (α = 0.93) and good test–retest reliability (pl = 0.74, p < 0.001).

#### Other pre-specified outcome measures

*Socio-demographic data* age, sex, educational level, income, marital status, number/age of children, and history of psychological treatment.

*Opinion of treatment scale,* adapted from Borkovec and Nau [59].

### Measures‑patients

#### Primary outcomes

*The eating attitudes test‐26* [60]. in its Spanish version [61]. *This scale is used to evaluate the patients*. It is a 26-item self-report that assesses attitudes toward eating. Items are rated on a 6-point Likert scale ranging from 1 (never) to 6 (always). The reliability analysis indicated good internal consistency [60, 62–65].

*Patient health questionnaire* [66]. in its Spanish version [67]. *This scale is used to evaluate the patients*. It assesses each of the nine DSM-IV criteria for depression through nine items. Items are rated on a 4-point Likert scale ranging from 0 (not at all) to 3 (nearly every day).

#### Secondary outcomes

*Overall anxiety severity and impairment scale* [68]. in its Spanish version [69]. *This scale is used to evaluate the patients.* It is a 5-item scale that assesses the severity and frequency of anxiety symptoms, behavioral avoidance, and the functional impairment related to anxiety. Items are rated on a 4-point Likert scale ranging from 0 to 4. It shows good psychometric properties in terms of test–retest reliability and internal consistency (α = 0.80).

*Validating and Invalidating responses scale* [70]. *This scale is used to evaluate the patients*. It is a 16-item scale that assesses the levels of perceived validation and invalidation of caregivers’ responses, divided into validating and invalidating responses. Items are rated on a 5-point Likert scale ranging from 0 (never) to 4 (almost always). Higher scores indicate greater perceived validation or invalidation of the responses of the caregiver being assessed.

*Lum emotional availability of parents* [71]. *This scale is used to evaluate the patients*. It is a 15-item questionnaire that assesses the emotional availability of mothers and fathers as perceived by the person assessing their relatives. Items are rated on a 6-point Likert scale ranging from 1 (never) to 6 (always). The psychometric properties are very good; for a clinical sample, excellent internal consistency is observed (for mother α = 0.92, and for father α = 0.93). In addition, it has adequate test–retest reliability for the mother's form (r = 0.92) and the father's form (r = 0.85).

### Data analyses

Regarding data analysis, the results of the pilot feasibility study using focus groups will be analyzed using thematic analysis in order to identify the topics that emerge from the focus groups [72]. Data reporting will be carried out following the COREQ guidelines [73]. In addition, qualitative research quality criteria recently developed by Levitt et al. [74] will be pursued in order to achieve what the authors refer to as methodological integrity in the qualitative field.

In the controlled clinical trial, the CONSORT guidelines [43] will be followed. First, participants' scores in the two conditions will be compared before the intervention to check that there are no significant differences between them on the outcome measures and that they are, therefore, comparable after randomization. ANOVAs will be conducted for continuous variables and Chi-square tests for categorical variables. For outcome measures at post-treatment, we will study whether the assumption of homoscedasticity is met with Levene's test. If this assumption is met, repeated-measures ANOVAs and F-tests will be used to compare the two experimental conditions. If the homoscedasticity assumption is not met, the Brown-Forsythe test will be applied. F-tests for statistical significance will be followed by post hoc comparisons. In particular, Tukey will be used when the homoscedasticity assumption is met, and Games-Howell if the homoscedasticity assumption is not met. Appropriate analyses will also be carried out to calculate intervention effect sizes and confidence intervals. The intention-to-treat principle will be used when analyzing pre- and post-treatment data and at 12-month follow-up, using mixed-effects models with full information and maximum likelihood estimation. To complement the results of ANOVAs and post hoc comparisons, effect sizes will be calculated using the standardized mean difference proposed by Cohen [75]. These effect sizes will be calculated to assess changes within and between groups, all based on a pooled standard deviation.

For the qualitative study, semi-structured in-depth interviews will be used. These interviews will follow the guidelines of Knox and Burkard [76]. The research design will be carried out following the criteria established by Cooke, Smith and Booth [40]. Data will be analyzed using the consensual qualitative research (CQR) method. Data reporting will be carried out following the COREQ guidelines [73]. Furthermore, we will attempt to meet the criteria for quality in qualitative research recently developed by Levitt et al. [74] in order to pursue what the authors refer to as methodological integrity in the qualitative field.

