### Sample size

To calculate the sample size, effect sizes found in previous studies on the topic have been considered. Grenyer et al. [30] tested a group psychoeducation protocol for caregivers of people with BPD in a controlled study that reports medium to large effect sizes (dyadic adjustment, *d* = 0.78; family empowerment, *d* = 1.4). Moreover, Grenyer obtained significant improvements on measures of illness burden between post-assessment and 12-month follow-up, with medium effects (*d* = 0.45). These effects are in line with the literature on psychological treatments for relatives of people with ED (Positive Caregiver Experience, *g* = -0.80) [14]. Given these data, an effect size of 0.50 is expected in the present study, adopting a conservative approach. Because our design includes two experimental conditions, t-tests are assumed for the statistical analyses. Considering an alpha of 0.05 and a statistical power of 0.80 in a two-tailed t-test, the total sample size needed to reach an effect size of 0.60 in loading is 90 participants (45 participants per experimental condition). To control for the maximum possible loss of subjects during treatment, based on the literature on previous programs for family members of BPD or ED patients, a dropout rate of 30% is expected [34–36]. Therefore, the required sample size should contain 124 participants in all (62 participants per group), as Fig. 1 shows. These calculations were carried out using the software program G*Power 3.1 [44].

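### Non-significant baseline tests are taken as proof that the arms are comparable, and no named analysis is said to condition on the baseline score

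*Protocol article*

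**What the plan says.** The Data analyses section of the protocol article opens the trial analysis with a comparison of the two conditions before the intervention, "to check that there are no significant differences between them on the outcome measures and that they are, therefore, comparable after randomization". The method is given as "ANOVAs will be conducted for continuous variables and Chi-square tests for categorical variables". No significance level, margin or interval is attached to the check, and nothing is said about what follows from either result.

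For the outcomes, if variances are homogeneous, "repeated-measures ANOVAs and F-tests will be used to compare the two experimental conditions"; otherwise the Brown-Forsythe test applies. The intention-to-treat analysis uses mixed-effects models on pre-treatment, post-treatment and 12-month data. Cohen's d, within and between groups, is based on a pooled standard deviation. A baseline covariate is not mentioned for any of these.

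The Sample size section gives the numbers that fix what the baseline tests can detect: "the required sample size should contain 124 participants in all (62 participants per group").

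**The concern.** The word linking the two halves of the baseline sentence turns a non-significant test into evidence of equivalence. Participants are randomised, so the null hypothesis of that test is true by design. A large p-value does not show that the realised imbalance is too small to matter, and a small one does not show that randomisation failed.

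The rule can therefore mislead in both directions. A moderate chance imbalance in burden or incidents is certified as comparability, while a sound trial tested on many baseline scores will often produce at least one significant difference.

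What is at stake is how the effect estimate reads given the imbalance that actually occurs, and the precision lost if a baseline score that is collected anyway is not used as a covariate.

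**Working it through.** **Inputs from the Sample size section.** 62 per arm randomised; 45 per arm before the dropout allowance; d = 0.60; two-sided alpha 0.05; power 0.80.

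**Assumptions, not in the document.** Alpha 0.05 for the baseline tests; pre-post correlation ρ of 0.3, 0.5 or 0.7; equal SDs before and after treatment; one score per measure.

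**The plan's own figure.** For a two-sided t-test at d = 0.60 and 80% power, the noncentral t gives 44.6, so 45 per arm (90 in all), with power 0.804. The stated 90 is reproduced.

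**1. What the check lets through.** With two groups, the ANOVA is a two-sided t-test. The largest non-significant observed difference at 62 per arm is

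t(0.975, 122) × √(2/62) = 1.980 × 0.1796 = 0.356 SD.

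That is 0.356/0.50 = 71% of the effect the plan says it expects and 0.356/0.60 = 59% of the effect behind the 90. An observed 0.50 SD gives t = 0.50/0.1796 = 2.78, p = 0.006, and is flagged.

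**2. How often chance alone triggers it.** Count: 6 incident counts + burden scale + 7 secondary family instruments + 5 patient instruments = 19. If independent, P(at least one p < 0.05) = 1 − 0.95^19 = 0.62. In a simulation with equally correlated normal scores it is 0.52 at correlation 0.3 and 0.41 at 0.5.

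**3. How common imbalances are on one measure.** From P(|D| > x) = 2[1 − Φ(x/0.1796)]: 0.2 SD or more, about 27%; 0.35 SD or more, about 5%; 0.5 SD or more, about 0.5%.

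**4. Effect of a realised imbalance δ = 0.35 SD.** The post-score contrast shifts by ρδ. The change contrast shifts by −(1 − ρ)δ. A baseline-adjusted contrast has no shift in expectation. For the conditional false-positive rate at n = 62 per arm:
- the post-score Z has mean ρδ/√(2/n) and SD √(1 − ρ²);
- the change-score Z has mean −(1 − ρ)δ/√(2(1 − ρ)·2/n) and SD √((1 + ρ)/2).

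| ρ | Post shift (SD) | Post rate | Change shift (SD) | Change rate |
|---|---|---|---|---|
| 0.3 | 0.11 | 8% | −0.25 | 16% |
| 0.5 | 0.18 | 13% | −0.18 | 13% |
| 0.7 | 0.25 | 20% | −0.11 | 10% |

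**5. Power at 45 per arm, d = 0.60.** The effective size is d for post scores, d/√(2(1 − ρ)) for change scores and d/√(1 − ρ²) with baseline adjustment.

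| ρ | Post score | Change score | Baseline-adjusted |
|---|---|---|---|
| 0.3 | 80% | 66% (size 0.507) | 84% (size 0.629) |
| 0.5 | 80% | 80% (size 0.600) | 90% (size 0.693) |
| 0.7 | 80% | 95% (size 0.775) | 98% (size 0.840) |

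Adjustment has the highest power in every row.

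**The case against.** The strongest defence is that the check drives nothing. The article attaches no consequence to it, and the baseline score is already used: it is one of the repeated measures, and the Objectives and hypotheses section defines effectiveness by differences between before and after. This is also a condensed article, and covariates and mixed-model terms are commonly left to an analysis plan. All of this stands as a limit on the harm. A baseline-constrained mixed model is not ruled out. But the faulty inference is stated in the article itself. A time-by-group contrast on a repeated measure uses baseline as a change score does, which leaves regression to the mean in the estimate, and the Brown-Forsythe test is introduced for post-treatment outcomes.

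Three stronger readings are tempting and are not supported.

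- A reader might infer that the tests miss a 0.5 SD imbalance about one time in five. The 21% is one minus power for a true population difference, which randomisation makes zero. An observed 0.5 SD at 62 per arm is always significant. The relevant figure is the 0.356 SD cut-off.
- A reader might infer that adjustment is withheld when the tests are non-significant, or that the trial is declared non-comparable after one significant result. The article says neither.
- A reader might infer that the effect estimates are biased. Over all randomisations, post-score and change-score contrasts are unbiased and hold 5% type I error. The rates in step 4 condition on an imbalance near the edge of the passing zone. Averaged over all imbalances that pass, the same formulas give rates below 5% for both contrasts.

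**Conclusion.** The point holds in a limited form. Inferring comparability from non-significance is a stated error, and the tests have no useful role in a randomised trial. At 62 per arm they certify any observed imbalance below about 0.36 SD, and across about 19 scores they raise at least one chance alarm with probability 0.41 to 0.62, depending on correlation.

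The consequence for the effect estimate is conditional: a shift of 0.11 to 0.25 SD given a 0.35 SD imbalance, with opposite signs for post-score and change contrasts. The more general loss is precision. Adjustment adds about 4 to 18 percentage points of power over post scores (84 − 80 and 98 − 80) and about 18 down to 3 over change scores (84 − 66 and 98 − 95).

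The cut-off rests on 62 per arm and an assumed two-sided 0.05. The shifts and power figures rest on assumed correlations of 0.3 to 0.7, and the power figures also on d = 0.60. The Sample size section also says that "an effect size of 0.50 is expected in the present study"; that conflict is a separate matter and does not affect the cut-off. The change is worth making because it is free, not because the planned tests are invalid.

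**What to change.** In the Data analyses section:

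1. Delete the baseline ANOVAs and chi-square tests and the conclusion drawn from them. Describe baseline by arm with means, SDs and counts.
2. State that every between-arm comparison includes the baseline value of that outcome as a covariate, or uses a mixed model with a common baseline mean across arms, whatever imbalance is observed.
3. Report between-arm effect sizes and confidence intervals from that model rather than from raw group differences.

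The cost is wording only. The Procedure section already has relatives and patients assessed before the intervention, so no extra data or visits are needed. If an analysis plan already specifies baseline adjustment, the article's text should be brought into line with it.

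### Two analyses on different sets of relatives are prescribed for the same post-treatment arm comparison, and the article does not say which one governs

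*Protocol article*

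**What the plan says.** The Data analyses section of the protocol article describes two routes to the post-treatment comparison.

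- **ANOVA route.** If Levene's test is satisfied, "repeated-measures ANOVAs and F-tests will be used to compare the two experimental conditions". Otherwise: "If the homoscedasticity assumption is not met, the Brown-Forsythe test will be applied". Post hoc comparisons follow.
- **Mixed-model route.** "The intention-to-treat principle will be used when analyzing pre- and post-treatment data and at 12-month follow-up", and this is to be done "using mixed-effects models with full information and maximum likelihood estimation".

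The text then returns to the first route for effect sizes: "To complement the results of ANOVAs and post hoc comparisons, effect sizes will be calculated using the standardized mean difference proposed by Cohen". It adds: "These effect sizes will be calculated to assess changes within and between groups, all based on a pooled standard deviation". A separate, general sentence promises effect sizes and confidence intervals without naming a method.

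The Methods paragraph of the Abstract states intention-to-treat for the data analysis without exception. The Sample size section plans 124 relatives (62 per arm) and says "a dropout rate of 30% is expected", in the context of loss during treatment.

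**The concern.** The two routes differ in whom they analyse and in what they assume about missing scores. A classical repeated-measures ANOVA on pre and post scores needs both scores from each relative. A full-information mixed model keeps every relative with a baseline score. Both are applied to the same pre-post data, and nothing says which result is the trial's answer. The only sentence that names a test for comparing the two conditions names the ANOVA. A reader following the text could therefore report an analysis of complete pairs as the main result of a trial described as intention-to-treat.

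The choice matters most if loss differs by arm in a way related to baseline burden. That is plausible here: the Interventions section sets 12 weekly two-hour sessions in FC: ED-PD against one three-hour session in TAU-O. If the more burdened relatives leave FC more often, those who remain start lower and have less room to regress towards the mean. That difference then enters the arm contrast.

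**Working it through.** **Inputs from the article.** 124 randomised, 62 per arm; 30% dropout; effect size 0.60 for the power calculation; two-sided alpha 0.05; power 0.80 (all Sample size section).

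**The plan's own figure.** An exact two-sample t-test at 0.60 SD needs 45 per arm (power 0.804), so the stated 90 evaluable relatives reproduces.

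**Analysis sets.**
- Mixed model: all 124 relatives with a baseline score.
- Repeated-measures ANOVA: 124 x 0.70 = 86.8, about 87 (62 x 0.70 = 43.4 per arm), if every dropout also lacks a post-treatment score. This is the worst case under the plan's 30%.

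**Bias of the complete-pairs contrast.** With two arms and two time points, the time-by-arm test is a t-test on change scores. The notation is:
- scores standardised to SD 1, with r the pre-post correlation;
- m(FC) and m(TAU) the mean baseline among retained relatives (0 if loss is unrelated to baseline);
- benefit written as TAU-O mean change minus FC mean change, true value d.

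Change regresses on baseline with slope r - 1, so the complete-pairs contrast has expectation

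d + (1 - r) x [m(FC) - m(TAU)].

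The observed difference in post-treatment scores alone has expectation

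d - r x [m(FC) - m(TAU)].

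**Assumed loss pattern (not in the article).** In FC, logit(loss) = -1 + baseline. This gives 1/(1 + e^2) = 12% at -1 SD and 1/(1 + e^0) = 50% at +1 SD. Integrating over a standard normal baseline gives 30% loss overall and m(FC) of about -0.26. In TAU-O, 30% loss at random gives m(TAU) = 0. The values r = 0.5 and 0.7 are also assumed.

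| Quantity, true d = 0.60 | r = 0.5 | r = 0.7 |
|---|---|---|
| Complete-pairs change contrast | 0.60 - 0.5 x 0.26 = 0.47 | 0.60 - 0.3 x 0.26 = 0.52 |
| Observed post-treatment difference | 0.60 + 0.5 x 0.26 = 0.73 | 0.60 + 0.7 x 0.26 = 0.78 |
| Full-information ML (simulated) | 0.60 | 0.60 |

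Simulation with 62 per arm and several thousand runs per scenario agrees: 0.47 to 0.48 at r = 0.5 and 0.52 to 0.53 at r = 0.7 for complete pairs.

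**Rejection rate with no true effect (simulated, nominal 5%).**
- Loss random, or dependent on baseline equally in both arms: about 5%, no bias.
- Pattern above: 7-9%.
- Loss dependent on baseline in opposite directions in the two arms, a deliberately strong assumption: 15-23% across runs. At r = 0.5 the bias is 0.5 x 2 x 0.26 = 0.26 SD in size.

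**The case against.** A reader might infer that the planned arm comparison simply is a completer analysis that breaks intention-to-treat. The article does not support that. It assigns intention-to-treat explicitly to mixed models with full-information maximum likelihood at pre-treatment, post-treatment and 12 months, so an analysis that honours the principle is in the plan.

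Four further objections stand:

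- Not every named quantity needs both scores. A between-group Cohen d at post-treatment, or a Brown-Forsythe test on post-treatment scores, needs only the post score. These still omit relatives without one.
- That the effect sizes come from complete pairs only is an inference. The text says they complement the ANOVA results and does not define their analysis set.
- Leaving treatment is not the same as missing the post-treatment assessment. The Procedure section does not limit reassessment to those who finish treatment, and the Study design section plans interviews with relatives who drop out. The 87 is therefore a worst case.
- The size of the bias rests on an assumed loss pattern. In the one-arm pattern it works against FC, so there it would not create a false claim of benefit.

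One objection does not stand: that priority between methods is a detail an article leaves to the analysis plan. The article states both methods for the same comparison and words the ANOVA as the test of the conditions. The conflict is in what is written, not in what is left out.

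**Conclusion.** The point holds as a conflict of analysis sets without a stated priority. The ANOVA strand, taken alone, does not meet the intention-to-treat principle stated in the Abstract and in Data analyses. The mixed-model strand does.

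How much this matters depends on the loss mechanism, which the documents cannot settle. It ranges from no bias (random loss, or the same dependence on baseline in both arms) to a loss of about 0.07 to 0.13 SD from a true 0.60 under the one-arm pattern. In that pattern the change contrast and the observed post-treatment difference err in opposite directions, so an ANOVA and a Cohen d meant to complement it could disagree for reasons unrelated to the treatment.

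The mixed model removes this bias only where loss is explained by observed scores. Loss that depends on the unseen post-treatment score would bias both routes.

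**What to change.** State in Data analyses that the FC minus TAU-O difference at post-treatment and at follow-up, its confidence interval and the between-arm standardised effect size come from the mixed-effects model. Fit that model to all randomised relatives, including those with a baseline score only. Label any repeated-measures ANOVA or Brown-Forsythe result a supportive analysis of relatives with available scores, and report how many relatives it includes in each arm.

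The cost is a few lines of wording. No new data are needed, the mixed model is already planned, and the article's Data Availability statement says the study is still in progress.
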